## Abstract

**Introduction::**

Physical and mental changes associated with aging commonly lead to a decrease in communication capacity, reducing social interactions and increasing loneliness. Computer classes for older adults make significant contributions to social and cognitive aspects of aging. Games in a virtual reality (VR) environment stimulate the practice of communicative and cognitive skills and might also bring benefits to older adults. Furthermore, it might help to initiate their contact to the modern technology. The purpose of this study protocol is to evaluate the effects of practicing VR games during computer classes on the level of loneliness of students of an elderly reference center.

**Methods and Analysis::**

This study will be a prospective longitudinal study with a randomised cross-over design, with subjects aged 50 years and older, of both genders, spontaneously enrolled in computer classes for beginners. Data collection will be done in 3 moments: moment 0 (T0) – at baseline; moment 1 (T1) – after 8 typical computer classes; and moment 2 (T2) – after 8 computer classes which include 15 minutes for practicing games in VR environment. A characterization questionnaire, the short version of the Short Social and Emotional Loneliness Scale for Adults (SELSA-S) and 3 games with VR (Random, MoviLetrando, and Reaction Time) will be used. For the intervention phase 4 other games will be used: Coincident Timing, Motor Skill Analyser, Labyrinth, and Fitts. The statistical analysis will compare the evolution in loneliness perception, performance, and reaction time during the practice of the games between the 3 moments of data collection. Performance and reaction time during the practice of the games will also be correlated to the loneliness perception.

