## Introduction

1

Individual aging, or senescence, is a progressive process that affects all systems structurally and functionally, compromising speed, accuracy, strength, stability, and coordination.^[1]^ These difficulties suggest differences between older and young adults regarding the ability to process information and learn.^[2]^ This can happen in both motor and cognitive tasks, leading to a decrease in the communication capacity of older adults, consequently reducing social interactions, and increasing loneliness.

Loneliness can be defined as perceived social isolation: the feeling of missing intimate interpersonal relationships (but not necessarily an actual lack of social interaction).^[3]^ With ageing, people become particularly vulnerable to loneliness due to deteriorating physical health, the death of spouses and partners, being more likely to live alone, and having fewer confiding relationships.^[4]^ Therefore, with ageing, people should learn how to use communication tools, which are new or already known, in different ways as an attempt to overcome loneliness.

Information and communication technologies (ICTs) are important instruments to access contemporary culture and to feel socially included. With the advent of mobile technology, the definition of communication and the means of social interaction are changing rapidly. Therefore, ICT can be an important tool to reduce loneliness among older adults.^[5]^

In general, the younger generation has confidence in using technology and assimilates the changes easily as, since their early years, they have explored electronic toys and/or played with mobile phones. However, the older generation, born before the development of the digital world, has more difficult in accessing these technologies.^[6]^ In addition, some elderly individuals may lack the motor skills to easily use digital devices.

Therefore, interventions to make ICT more accessible for older adults must focus on helping them acquire knowledge needed to maximize motor performance and social interaction, as both cognitive and motor skill are required to readily use ICT devices. Although they experience functional loss, older adults have the capacity to acquire new abilities and their performance can be similar to young adults.^[7]^

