Considering the settings presented, we believe that motor and cognitive ability acquired through VR games might facilitate computer utilization, which is a valuable communication tool.^[17]^ Therefore, we intend to assess, through a loneliness scale, a group of older adults that are initiating computer classes for beginners. The effects of practicing games using VR within computer classes will be compared to the impact of conventional computer classes. Games with VR, requiring a variety of different motor and cognitive abilities will be used to identify whether evolution in loneliness, is related to the practice of tasks using virtual ICTs. We hypothesized that the practice of VR games added to conventional computer classes will lead to an improvement in motor ability and less loneliness of older adults.

Thus, the main objective is to evaluate the effects of practicing games in a VR environment during computer classes on loneliness among students of an elderly reference center (ERC). Moreover, in students initiating computer classes for seniors, we aim to: evaluate the evolution in time of response during the practice of VR games; evaluate the evolution in performance of practice of VR games; and evaluate the relation between motor ability to loneliness.

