### Instruments

2.7

Instruments for assessment

A characterization questionnaire with information on gender, age, education, marital status, and use of computer and mobile phone will be used to characterize and homogenize the sample. Scores on the Mini-Mental Status Exam,^[20,21]^ which quickly screens and evaluates cognitive function, will be used as an exclusion criterion.

Evaluating the mood of participants may aid in evaluating their performance during the games. This hypothesis is based on findings of a negative correlation between mood and the sensory and motor functioning of subjects, suggesting that low mood might interfere with functional balance.^[25]^ Therefore, the Brunel Mood Scale was administered.

To evaluate loneliness, the Portuguese version of the short Social and Emotional Loneliness Scale for Adults, SELSA-S,^[22]^ validated for the elderly population, was used.

The questionnaires will be, preferably, filled out in an electronic format developed through Epi Info, which allows building questionnaires in a quick way and was developed by the Center of Diseases Control.^[26]^ Filling the forms directly on the computer allows defining answers that are mandatory, avoiding questions without answers. The answers will be exported to Microsoft Excel, avoiding typos.

The games used in the study, Random, MoviLetrando, and Reaction Time, will be used to assess performance through reaction time, hits, and misses.

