### Data analysis

8.3

Excel and SPSS version 2.1 for Windows will be used for data preparation and analysis. The significance level will be *P* ≤ 0.05.

The data will be presented as means and standard deviations and in frequency tables. Before the data analysis, the normality of all variables will be evaluated for skewness and kurtosis. To compare participants’ mood and loneliness, paired *t* tests, Kruskal–Wallis tests, Mann–Whitney *U* tests, or Pearson correlation coefficients will be used. The analysis will be blinded and will compare the 3 moments of data collection and the 2 groups (G1 and G2). To guard against the possibility of type 1 errors from making too many post hoc comparisons, we will carry out only those comparisons that have been planned based on our hypotheses.

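### The secondary aim of relating motor ability to loneliness relies on a correlation with no stated adjustment for age, although the protocol links ageing to both, so age alone could produce an association

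*Protocol article*

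**What the plan says.** The Introduction of the protocol article lists among its further aims to "evaluate the relation between motor ability to loneliness", and the Discussion repeats it. The abstract (Methods and Analysis) gives the method: "Performance and reaction time during the practice of the games will also be correlated to the loneliness perception". It names no coefficient and no covariate.

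Data analysis (section 8.3) lists the techniques: "To compare participants’ mood and loneliness, paired *t* tests, Kruskal–Wallis tests, Mann–Whitney *U* tests, or Pearson correlation coefficients will be used". Pearson is the only measure of association in that list, and the sentence ties it to mood and loneliness, not to motor ability. No partial correlation, regression or covariate appears anywhere in the article.

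On age, the Introduction says that ageing "is a progressive process that affects all systems structurally and functionally, compromising speed, accuracy, strength, stability, and coordination". It also says: "With ageing, people become particularly vulnerable to loneliness due to deteriorating physical health, the death of spouses and partners, being more likely to live alone". The abstract describes a sample "with subjects aged 50 years and older, of both genders, spontaneously enrolled in computer classes for beginners". Instruments (section 2.7) provides for "A characterization questionnaire with information on gender, age, education, marital status, and use of computer and mobile phone", but gives these data only a descriptive and homogenising role, with no part in the analysis.

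**The concern.** On the protocol's own account, age lies behind both variables in the correlation. Some of the routes it gives from age to loneliness, namely bereavement and living alone, do not pass through motor ability. Older participants would then tend to be both slower in the games and lonelier, and a raw coefficient would pick that up even if motor ability had no bearing on loneliness. With no upper age limit, there is room for age to vary enough to matter.

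What is at stake is a supporting claim. The hypothesis pairs better motor ability with less loneliness, and this correlation is the planned evidence that ties the two together. If age alone can produce it, a significant result could be read as support for a mechanism that the data do not show. The protocol names the likely confounder and measures it, but does not say that it will be used.

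**Working it through.** The documents give no figure for this correlation and no age correlations, so there is no stated result to reproduce. The check asks what an unadjusted test does when age is the only connection.

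**Inputs from the protocol article**
- Significance level 0.05 (Data analysis). Sidedness is not stated; two-sided is assumed.
- Minimum sample of 23 (Study population, section 2.1).
- Maximum sample of 60: 6 classes × at most 10 students (Intervention, section 2.5).

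**Assumptions**
- a = correlation of age with motor ability, and b = correlation of age with loneliness. The main range runs from (0.3, 0.2) to (0.5, 0.3), with (0.2, 0.2) and (0.5, 0.5) shown as outer cases.
- Normal variables and no direct link between motor ability and loneliness.

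**Step 1: induced correlation.** With motor = a·age + noise and loneliness = b·age + noise, the marginal correlation is r = a × b. This gives 0.3 × 0.2 = 0.06, 0.4 × 0.3 = 0.12 and 0.5 × 0.3 = 0.15. The partial correlation given age is 0.

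**Step 2: size needed for significance.** Critical |r| = t / √(df + t²), with df = n − 2.
- n = 23: 2.080 / √(21 + 2.080²) = 0.413.
- n = 60: 2.002 / √(58 + 2.002²) = 0.254.

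**Step 3: rejection rates with no direct link.** These come from simulation with 40,000 replicates per setting; repeat runs differ by a few tenths of a percentage point. The adjusted test uses r(M,L·A) = (r_ML − r_MA·r_LA) / √[(1 − r_MA²)(1 − r_LA²)], where M is motor ability, L loneliness and A age, with one degree of freedom fewer.

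| a, b | induced r | raw Pearson, n = 23 | raw Pearson, n = 60 | age-adjusted, both n |
|---|---|---|---|---|
| 0.2, 0.2 | 0.04 | 5.4% | 6.1% | about 5% |
| 0.3, 0.2 | 0.06 | 5.8% | 7.7% | about 5% |
| 0.4, 0.3 | 0.12 | 8.4% | 15% | about 5% |
| 0.5, 0.3 | 0.15 | 10.4% | 21.0% | about 5% |
| 0.5, 0.5 | 0.25 | 21.1% | 49.1% | about 5% |

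**Step 4: would a within-person analysis be enough by itself?** Using each person's change across the three moments removes age, which is essentially fixed over 16 classes. It brings another risk: game scores and loneliness may both drift over time. With no true link, an assumed within-person correlation of 0.7 in each variable and an assumed trend of 0.2 SD per moment in both, the within-person test without a term for moment rejects about 12% (n = 23) and 25% (n = 60). With that term it rejects about 5%. At 0.1 SD per moment the inflation without the term is slight, about 5.3% and 6.4%.

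**The case against.** The best defence is that the method is partly inferred. Section 8.3 attaches Pearson to mood and loneliness, and the abstract says neither Pearson nor unadjusted. The article is a condensed account, and an analysis plan that is not shown could add covariates. This stands as a limit on how firmly the point can be put. It does not remove the point: a correlation is the stated method for this aim, and the stated role of the age variable is descriptive.

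A second defence is that ageing may act on loneliness through motor decline, which the Introduction also suggests. That does not rescue the raw coefficient. Adjusting for age keeps any real link from motor ability to loneliness and removes only the shared age component.

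A third is that the effect is modest. This is fair. In the main assumed range, about 79–94% of trials with no direct link would still give a non-significant result, and with weak age effects at n = 23 the inflation is negligible.

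Two stronger readings are tempting and are not supported:
- A reader might infer that the three moments will be pooled in one correlation, treating repeated measurements as independent. The article does not say so. Section 8.3 speaks of comparing the moments, and a coefficient at each moment or on changes fits the text equally well.
- A reader might say that the correlation fails because it cannot show whether the evolution of loneliness is related to practising the games. That is a separate question, which belongs to the comparison of groups and moments. The aim at issue asks for an association, and a correlation does address it.

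Prior computer use is a weaker candidate than age as a confounder: all participants are beginners, and the article gives no comparable statement about it.

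**Conclusion.** The concern holds in a limited form. The protocol plans to relate motor ability to loneliness by a correlation with no stated adjustment, while naming ageing behind both. If age is the only connection, and its correlations with the two variables lie between 0.3 and 0.2 and 0.5 and 0.3, the raw r is 0.06 to 0.15 and the nominal 5% test rejects about 6–10% at n = 23 and 7–21% at n = 60. These age correlations are assumptions. Weaker ones make the problem trivial; 0.5 and 0.5 would raise rejection to about 21% and 49%.

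The trial could report a spurious link; it cannot be said that it would. The aim is secondary and observational, and the randomised comparison of conventional classes with classes that include games does not depend on it.

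**What to change.** State in Data analysis that the conclusion on motor ability and loneliness rests on an age-adjusted analysis: either a partial correlation given age, or a regression of SELSA-S on game performance with age as a covariate. Compute it separately at each moment, and say that the moments will not be pooled as independent observations. Report the raw coefficient as descriptive and name which coefficient it is.

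If the report is also to claim that change in motor ability goes with change in loneliness, use within-person change across the three moments in a model with a participant effect, a term for moment and a term for the phase received (conventional or VR classes). Age, education and computer use do nothing for that within-person coefficient. The term for moment guards against shared time trends, as step 4 of the working shows.

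The cost is one degree of freedom for age and a little more analysis work; age is already collected. With as few as 23 participants, the covariate set should be kept short, with age first.

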**Ethics and Dissemination::**

The protocol is approved by the host institution's ethics committee under the number 52305215.3.0000.0082. Results will be disseminated via peer-reviewed journal articles and conferences. This clinical trial is registered at ClinicalTrials.gov identifier: NCT02798081.

## Introduction

1

Individual aging, or senescence, is a progressive process that affects all systems structurally and functionally, compromising speed, accuracy, strength, stability, and coordination.^[1]^ These difficulties suggest differences between older and young adults regarding the ability to process information and learn.^[2]^ This can happen in both motor and cognitive tasks, leading to a decrease in the communication capacity of older adults, consequently reducing social interactions, and increasing loneliness.

Loneliness can be defined as perceived social isolation: the feeling of missing intimate interpersonal relationships (but not necessarily an actual lack of social interaction).^[3]^ With ageing, people become particularly vulnerable to loneliness due to deteriorating physical health, the death of spouses and partners, being more likely to live alone, and having fewer confiding relationships.^[4]^ Therefore, with ageing, people should learn how to use communication tools, which are new or already known, in different ways as an attempt to overcome loneliness.

Information and communication technologies (ICTs) are important instruments to access contemporary culture and to feel socially included. With the advent of mobile technology, the definition of communication and the means of social interaction are changing rapidly. Therefore, ICT can be an important tool to reduce loneliness among older adults.^[5]^

In general, the younger generation has confidence in using technology and assimilates the changes easily as, since their early years, they have explored electronic toys and/or played with mobile phones. However, the older generation, born before the development of the digital world, has more difficult in accessing these technologies.^[6]^ In addition, some elderly individuals may lack the motor skills to easily use digital devices.

Therefore, interventions to make ICT more accessible for older adults must focus on helping them acquire knowledge needed to maximize motor performance and social interaction, as both cognitive and motor skill are required to readily use ICT devices. Although they experience functional loss, older adults have the capacity to acquire new abilities and their performance can be similar to young adults.^[7]^

Research on computer classes to elderly, shows that, given appropriate structures of teaching and learning specific to older adults, elderly individuals can learn these skills even though aging can make it more challenging.^[6]^ The psychosocial impact on older adults who learned how to use the Internet was positive, showing a trend toward decreased loneliness and depression.^[8]^ One possibility for helping older adults learn effective use of ICT is via virtual reality (VR), which in general is a useful tool to study, evaluate, and rehabilitate cognitive processes and functional activities.^[9]^

VR allows the performance of new tasks and might stimulate the practice of communicative and cognitive skills, benefiting functional improvement and initiating the contact of older adults with the modern technology. Still, game software can stimulate and, also, store responses, differently from other preconized methods.^[10]^ Virtual games and virtual environments can be used as physical, cognitive, or psychological interventions to enable function and fun for different people.^[11]^ By using VR, it is possible to promote flexibility and control in task administration, increasing the chance of transferring an acquired ability in an efficient and safe way.^[12]^

Regarding VR utilization for older adults, there are studies on postural control,^[13]^ balance, fall prevention, physical activity incentives, and functional performance.^[14]^ The positive effects of using a VR game included improving physical function, decreasing depression, and increasing cognition and quality of life in older adults. Improved socialization and motivation to exercise were also reported.^[15]^ Most of the studies that assess older adults in virtual tasks were done with older adults with acquired physical and cognitive diseases, and the healthy older adults were only part of the control group.^[16]^ However, the use of VR as a means of facilitating the use of computers and reducing loneliness of healthy older adults is scarce.

Considering the settings presented, we believe that motor and cognitive ability acquired through VR games might facilitate computer utilization, which is a valuable communication tool.^[17]^ Therefore, we intend to assess, through a loneliness scale, a group of older adults that are initiating computer classes for beginners. The effects of practicing games using VR within computer classes will be compared to the impact of conventional computer classes. Games with VR, requiring a variety of different motor and cognitive abilities will be used to identify whether evolution in loneliness, is related to the practice of tasks using virtual ICTs. We hypothesized that the practice of VR games added to conventional computer classes will lead to an improvement in motor ability and less loneliness of older adults.

Thus, the main objective is to evaluate the effects of practicing games in a VR environment during computer classes on loneliness among students of an elderly reference center (ERC). Moreover, in students initiating computer classes for seniors, we aim to: evaluate the evolution in time of response during the practice of VR games; evaluate the evolution in performance of practice of VR games; and evaluate the relation between motor ability to loneliness.

## Method

2

This study protocol followed the Stardard Protocol Items for Randomized Trials (SPIRIT).^[18]^ This study will be a prospective longitudinal study with a randomized cross-over design which will use games in a VR environment within computer classes to reduce loneliness among students at an ERC.

### Study population

2.1

It will be a convenience sample. The participants will be students in beginning level computer classes for seniors in the CRI in Ribeirão Pires, Sao Paulo, Brazil.

Because no study was found using the short version of the Social and Emotional Loneliness Scale for Adults (SELSA-S) before and after any intervention, sample calculation was not possible. However, there will be a minimum of 23 participants in this study, based on the largest sample that used VR in older adults found in the literature.^[13]^

The CRI Ribeirão Pires offers cultural, sportive, and intellectual activities for people over 50 years old, as used in the multicenter Studies on Global Ageing and Adult Health project of the WHO.^[19]^

### Inclusion and exclusion criteria

2.2

Initially, all students from beginning level computer classes for seniors at the CRI in Ribeirão Pires will be invited to participate.

Those who attend less than 75% of the classes between the assessments and/or do not complete the 3 moments of assessment will be excluded from the research. Individuals with motor impairment of the upper limbs which prevents them from practicing the games or a score lower than 23 in the mini-mental exam^[20,21]^ will also be excluded.

Any CRI student who is absent from class 3 times without a plausible excuse is excluded from the course and, therefore, will be excluded from the study. This helps ensure intervention adherence.

To reduce the likelihood that any student will feel harmed, the same intervention will be offered to all the participants. Those who match the exclusion criteria, but are willing to participate, will be excluded during data analysis.

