### Expected risks

2.3

The intervention proposed here generates minimal risks, as it involves noninvasive measurements. The informatics classes, as well as game practicing, will be done in the usual classroom. If the participant feels any discomfort, the proposed tasks must be stopped and the participant will be aided by the responsible professionals. Data will be collected in a private room, in the same place the participants have the informatics classes, attended only by the researchers and professionals skilled to help during its execution.

Although the procedure is noninvasive and the risks are minimal, the possible risks to physical or mental health are: eye strain due to sustained computer use, imbalance or pain during the movements imposed by the virtual games, or feeling sick or tired. Some embarrassment for not being able to or not understanding how to play the games may also happen. In any of these cases, the participant may withdraw from participation.

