### Intervention

2.5

There are 6 groups of computer classes for beginners offered by CRI, with a maximum of 10 students each. The classes last 2 hours, twice a week and include basic computer operations, the use of Word programs and introduction to the Internet.

For the intervention, the 6 classes of computer lessons for beginners will be randomly assigned into 2 groups, group 1 (G1) and group 2 (G2), with the same number of classes for each group.

The intervention will be divided into 2 phases, as shown in Fig. 1. In phase 1, G1 will have 8 conventional computer classes, while G2 will have 8 computer classes which will include 15 minutes of practicing games in a VR environment, using a physical interface (keyboard or mouse). In phase 2, intervention will be crossed between the groups. Therefore, G2 will have 8 conventional computer classes, while G1 will have 8 computer classes which will include 15 minutes of computer game practice. The games used for intervention (Labyrinth, Fitts, Motor Skill Analyzer [MOSKA], and Timing Coincident) will be described in the section Games for training.

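### Excluding students for attendance, expulsion or a missed assessment confines the comparison to completers and discards collected scores; the direction of any bias is unknown

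*Protocol article*

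**What the plan says.** Section 2.2 (Inclusion and exclusion criteria) gives three routes out of the study that depend on what happens during the course.

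- Attendance and completion: "Those who attend less than 75% of the classes between the assessments and/or do not complete the 3 moments of assessment will be excluded".
- Expulsion: a student who "is absent from class 3 times without a plausible excuse is excluded from the course and, therefore, will be excluded from the study".
- Handling of those who stay: "Those who match the exclusion criteria, but are willing to participate, will be excluded during data analysis". This sentence makes no distinction between baseline criteria and those met later.

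The same section has two other criteria, a Mini-Mental score below 23 and upper-limb impairment that prevents play. Neither depends on attendance or completion, and they are not at issue here.

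Section 2.5 says that "the 6 classes of computer lessons for beginners will be randomly assigned into 2 groups", and that the groups then differ by phase: "In phase 1, G1 will have 8 conventional computer classes, while G2 will have 8 computer classes which will include 15 minutes of practicing games", with the conditions crossed in phase 2. Section 2.6 places T1 and T2 after phases 1 and 2. Section 8.3 compares the three moments and the two groups. No analysis of all randomised students is described.

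Section 2.3 lists discomfort, tiredness and embarrassment with the games as possible risks and adds: "In any of these cases, the participant may withdraw from participation". Section 2.4 expects the games to affect motivation.

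**The concern.** Attendance between assessments and completion of T1 and T2 are observed while G1 and G2 are on different conditions. If the condition influences who stays, the students left in G1 and G2 are no longer the groups that randomisation formed, and a difference at T1 may partly reflect who was removed. Sections 2.3 and 2.4 give plausible links between the games and staying or leaving.

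The rule also wastes data. A student with T0 and T1 scores drops out of the phase 1 comparison merely because T2 is missing, and a poor attender with all three scores is deleted altogether. With a stated minimum of 23 students (section 2.1) and at most 60 (section 2.5), each deletion costs precision.

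This is a rule the protocol fixes, not a detail left for an analysis plan.

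**Working it through.** **Timing.** The article does not date the randomisation. The order still follows from sections 2.2, 2.5 and 2.6 read together: the attendance and completion criteria can be met only during or after phases whose content is set by the allocated sequence.

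**The plan's own figure.** The minimum of 23 is taken from an earlier study, with no effect size, SD or power, so no formula reproduces it. The point does not depend on it.

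**How easily the rule is triggered.**
- 75% of 8 classes is 0.75 × 8 = 6, so missing 3 of 8 (5/8 = 62.5% attended) excludes a student.
- If the 3 unexcused absences are counted over all 16 classes, expulsion occurs at 13/16 = 81% attendance. That can remove students who pass the 75% rule.
- Maximum enrolment is 6 × 10 = 60. Assume independent absences with probability p per class, and let a = P(at least 3 of 8 missed). The share removed in either phase is 1 − (1 − a)².

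| p (assumed) | a | Removed | Kept of 60 |
|---|---|---|---|
| 5% | 0.006 | 1.2% | 59.3 |
| 10% | 0.038 | 7.5% | 55.5 |
| 15% | 0.105 | 19.9% | 48.0 |
| 20% | 0.203 | 36.5% | 38.1 |

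**Possible bias in G1 versus G2 at T1.** All inputs are assumptions: no true effect, 30 per group, T0–T1 correlation 0.7, adjustment for T0, clustering by class ignored. Loss occurs only in the third with the worst loneliness change given T0.
- Residual SD: √(1 − 0.7²) = 0.714.
- Mean of the upper third of a standard normal: 0.3636 / (1/3) = 1.091. In SD units of the score this is 1.091 × 0.714 = 0.779.
- If a fraction q of that third leaves a group, the mean of those who stay shifts by −(q/3 × 0.779)/(1 − q/3). This gives −0.071 for q = 0.25, −0.156 for q = 0.5 and −0.260 for q = 0.75.
- Bias is the shift in the VR group minus the shift in the conventional group. Negative values favour VR.

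Simulation (4,000 trials per row; ranges are over repeat runs) agrees:

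| q in VR | q in conventional | Formula | Simulated bias (SD) | Type I error |
|---|---|---|---|---|
| 0 | 0 | 0 | 0.00 | 5.3% |
| 0.25 | 0 | −0.071 | −0.069 | 6.5% |
| 0.5 | 0 | −0.156 | −0.155 to −0.158 | 12.9–13.4% |
| 0.75 | 0 | −0.260 | −0.258 to −0.261 | 26.0–27.0% |
| 0.5 | 0.25 | −0.085 | −0.086 | 7.2% |
| 0.5 | 0.5 | 0 | 0.00 | 4.7% |
| 0 | 0.5 | +0.156 | +0.153 | 12.6% |

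**Possible bias in the within-person contrast.** Assume 60 randomised, independent period changes with SD 1, no true effect, and completers only.
- Exclusion unrelated to outcome: bias about 0, type I error about 5%.
- VR-phase log-odds of exclusion rising by 0.5 to 1.0 per SD of worse change: bias −0.05 to −0.12 SD (6% to 9%) at 10% base exclusion per phase, and −0.10 to −0.21 SD (7% to 15%) at 20%.
- The set-up is symmetric, so placing the selective loss in the conventional phase reverses the sign.

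**The case against.** A reader might infer that the rule makes VR look better, because it deletes those who tolerated the games badly. The documents do not support that.

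- Section 2.3 calls the risks minimal and possible and says only that a participant may withdraw. It gives no rate and does not say that the games are expected to cause withdrawal.
- Several of those risks are not specific to the VR phase. Training games use keyboard or mouse. The game described as played by arm and hand movement without a device is MoviLetrando, an assessment game that both groups play at all three moments. Eye strain is put down to computer use, which both conditions share. The conditions differ by 15 minutes of a 2-hour class.
- Section 2.4 expects the games to be enjoyable and motivating, so disengaged students could equally leave the conventional phase. That would bias against VR.
- Nothing in the article says that lonelier students stop attending. If they do so equally under both conditions, a null comparison is not biased, as the equal-loss row shows.

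Two further objections stand in part. A within-person cross-over contrast is less exposed than a parallel one, but it is not immune, and the G1 versus G2 comparison at T1 is parallel. Expulsion after three unexcused absences is the centre's rule for all its students. The study still chooses whether to go on following and analysing them.

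Section 2.2 says that the absence rule supports adherence. Encouraging attendance is reasonable, but removing non-attenders from the analysis does not improve it.

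**Conclusion.** The point holds in a limited form and should be fixed. The rule confines the group and phase comparisons to completers, discards scores already collected, and leaves room for selection related to condition. That much follows from the text, apart from the necessary inference about the timing of allocation.

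Size and direction do not follow from the text. Under the stated assumptions, bias is about −0.16 SD with 13% type I error if half of the worst third leaves the VR group only. It is about zero with 5% if loss is equal, and about +0.15 SD with 13% if only the conventional group loses them. Heavier or lighter loss widens or narrows that range. The illustration ignores clustering by class, and the pattern of loss is assumed throughout. The loss of precision is certain for every student deleted with usable scores, but their number is unknown.

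**What to change.** - Restrict exclusions from the analysis to criteria known at T0: the Mini-Mental score and upper-limb impairment, with the latter recorded at T0.
- Analyse every eligible student in the sequence to which their class was randomised, whatever the attendance. Use all available T0, T1 and T2 scores in a mixed model with treatment, period, sequence and class, allowing for repeated scores on the same student.
- Ask students who leave the course, and still consent, to complete the SELSA-S at the planned moments. The model recovers students whose scores exist but are now deleted. It does not correct loss that depends on unseen scores: where T1 is missing because of the T1 value itself, adjusting for T0 leaves essentially the same bias.
- Report exclusions and missing assessments by sequence and phase.
- Keep the 75%-attendance completer set as a sensitivity analysis.

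The cost is a change of protocol wording and a few extra questionnaires. The downside is that the estimate then includes poor attenders and may be slightly smaller.
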